10.2.1.2 Solicited Adverse Events Evaluations

Pre-treatment symptoms/conditions/adverse events must be graded at baseline and at each evaluation according to the test schedule in Section 4.0. Grading is per CTCAE v5.0 unless alternate grading is indicated in the table below:

| **CTCAE** **System Organ Class (SOC)** | **Adverse event/ Symptoms** | **CTCAE Grade at which the event will not be reported in an expedited manner^1^** |
| --- | --- | --- |
| General disorders and administrations site conditions | Fatigue | ≤Grade 3 |
|  | Pain | ≤Grade 3 |
|  | Dry eye | ≤Grade 3 |
| Skin and subcutaneous tissue disorders | Alopecia | ≤Grade 2 |
|  | Mucositis oral | ≤Grade 3 |
| Gastrointestinal disorders (GI) | Vomiting | ≤Grade 3 |
|  | Esophagitis | ≤Grade 3 |
|  | Dysphagia | ≤Grade 3 |
|  | Constipation | ≤Grade 3 |
|  | Nausea | ≤Grade 3 |
|  | Diarrhea | ≤Grade 3 |
|  | Dry mouth | ≤Grade 4 |
| Injury, poisoning and procedural complications | Dermatitis radiation | ≤Grade 3 |

#### 10.2.2 Serious Adverse Events

10.2.2.1 Site Requirements for Reporting SAEs

From the time of registration until ≤ 30 days after the administration of the last dose of study drug/agent or therapy, or until a new anti-cancer treatment starts (whichever occurs first), the Site Principal Investigator (PI) is responsible for ensuring that all SAEs (observed by study team, provided by external sources, etc.) are reported immediately to the sponsor, unless explicitly stated otherwise in table in Section 10.2.1.2

Any SAEs that occur when the patient is in event monitoring are not subject to being reported (expeditiously or otherwise) on this study unless they occur ≤ 30 days after the last dose of radiation the patient receives per protocol AND the patient has not started a new non-study anti-cancer treatment.

In addition to reporting to Mayo Clinic, the investigator is responsible for reporting to their appropriate IRB/IEC in accordance with local regulatory requirements and procedures.

Initial Reporting:

The investigator/study team must report SAEs as follows:

- - - All SAEs must be immediately submitted to Mayo Clinic following the study team’s knowledge of the event via the iMedidata Rave “Adverse Events” eCRF.

NOTES: This eCRF will generate the “SAE: Event Information” eCRF when the event is indicated as “serious.” Information documented on the iMedidata Rave “SAE: Event Information” eCRF must be consistent with that recorded on the source document.

Once the SAE information has been captured and submitted in iMedidata Rave, a report can be generated. A copy of this completed report must be kept within the study file at the study site.

- - - - The investigator must assess whether the SAE is possibly related to the investigational product.
      - The investigator is expected to follow reported SAEs until stabilization, resolution, or patient death. (See section below on Follow-Up Reporting.)

Follow-Up Reporting:

New information relating to a previously reported SAE needs to be submitted to Mayo Clinic:

- - - - Immediately upon site becoming aware of updated information
      - Sites may be required to:
- Provide additional information including but not limited to discharge summaries, medical records, etc.
- Query external locations for additional information if events occurred outside the participating site (i.e., Hospitalization records)
- Respond to Sponsor query(ies) if additional information is needed
  - - - All SAEs regardless of relation to study intervention will be followed until resolution to ≤ Grade 1 or baseline and/or deemed clinically insignificant, a new anti-cancer treatment starts, the patient is moved into event monitoring, or death whichever occurs first.
      - Revise the previously documented SAE on the appropriate iMedidata Rave eCRF.

NOTES: Information documented on the iMedidata Rave eCRF must be consistent with that recorded on the source document.

Once the updated SAE information has been captured and submitted in iMedidata Rave, a report can be generated. A copy of this updated report must be kept within the study file at the study site.

NOTE: Refer to **Section 10.2.3** for additional reporting requirements.

**Table 10.2.2.2 Expedited Reporting Requirements for Adverse Events/Serious Adverse Events**

| **EXPEDITED REPORTING REQUIREMENTS FOR SERIOUS ADVERSE EVENTS  (21 CFR Part 312)**  Investigators MUST immediately report to Mayo Clinic **ANY** Serious Adverse Events (SAE), whether or not they are considered related to the investigational agent(s)/intervention (21 CFR 312.64).  Mayo Clinic will report to FDA, per regulations [21 CFR 312.32(c)(d)].  The definition of a SAE can be found in **Section 10.1.3**.  Detailed site requirements for reporting SAEs can be found in **Section 10.2.2.1**. | | | |
| --- | --- | --- | --- |
| **Initial Reporting** | | **Follow-up Reporting** | |
| **HOSPITALIZATION**  **≥24 hours**  (Any Grade and/or Attribution) | **IMMEDIATELY** upon study team’s awareness of event.  (Not to exceed 24 hours.) | **HOSPITALIZATION**  **≥24 hours**  (Any Grade and/or Attribution) | **IMMEDIATELY** upon receiving any updated information regarding event.  (Not to exceed 24 hours.) |
| **GRADE 3**  Attribution of Possible, Probable, or Definite |  | **GRADE 3**  Attribution of Possible, Probable, or Definite |  |
| **GRADES 4 AND 5**  Regardless of Attribution |  | **GRADES 4 AND 5**  Regardless of Attribution |  |
| **Refer to Section 10.2.3 for detailed reporting requirements related to Important Medical Events (IME), Adverse Events of Special Interest (AESI), >30 days post treatment, and Pregnancy**. | | | |

Offline reporting when iMedidata Rave is unavailable:

If the iMedidata Rave system is unavailable to the site staff to report the SAE, the information is to be reported to Mayo Clinic by completing, scanning, and submitting a hard copy of the “Adverse Events” CRF and related “SAE: Event Information” CRFs within 24 hours of the investigator’s knowledge of the event. See the study forms packet for printable copy of these forms. Completed forms are to be submitted to [[contact]](mailto:[contact]).

For studies where the first notification of a SAE is reported to Mayo Clinic using the Offline reporting instructions, the data must be entered into iMedidata Rave when the system is again available. The originally submitted forms and the email correspondence must be kept within the study file at the study site.

10.2.2.3 Exceptions for Site(s) Regarding Expedited Reporting Timelines for SAEs

For this protocol only, the following AEs/Grades are expected to occur within this population and do not require Expedited Reporting. These events must still be reported via iMedidata Rave (see **Section 10.2.1.1**):

- - - - Specific protocol exceptions to expedited reporting should be reported immediately by investigators **ONLY** if they exceed the expected grade of the event.

| **CTCAE System Organ Class (SOC)** | **Adverse event/ Symptoms** | **CTCAE Grade at which the event will not be reported in an expedited manner^1^** |
| --- | --- | --- |
| General disorders and administrations site conditions | Fatigue | ≤Grade 3 |
|  | Pain | ≤Grade 3 |
|  | Dry eye | ≤Grade 3 |
| Skin and subcutaneous tissue disorders | Alopecia | ≤Grade 2 |
|  | Mucositis oral | ≤Grade 3 |
| Gastrointestinal disorders (GI) | Vomiting | ≤Grade 3 |
|  | Esophagitis | ≤Grade 3 |
|  | Dysphagia | ≤Grade 3 |
|  | Constipation | ≤Grade 3 |
|  | Nausea | ≤Grade 3 |
|  | Diarrhea | ≤Grade 3 |
|  | Dry mouth | ≤Grade 4 |
| Injury, poisoning and procedural complications | Dermatitis radiation | ≤Grade 3 |

*These exceptions only apply if the AE does not result in hospitalization. If the AE results in hospitalization, then the standard expedited AEs reporting requirements must be followed. The following hospitalizations are not considered to be SAEs because there is no “AE” (i.e., there is no untoward medical occurrence) associated with the hospitalization:

- Hospitalizations for respite care.
- Planned hospitalizations required by the protocol.
- Hospitalization planned before informed consent (where the condition requiring the hospitalization has not changed post study intervention).
- Hospitalization for elective procedures unrelated to the current disease and/or treatment on this trial.
- Hospitalization for administration of study intervention.
- Hospitalization for routine maintenance of a device (e.g., battery replacement) that was in place before study entry.
- Hospitalization or other serious outcomes for signs and symptoms of progression of the cancer.

#### 10.2.3 Other Reporting

10.2.3.1 >30 Days Post Treatment

Immediately, upon study team’s awareness of event, submit initial and follow-up (as applicable) reporting as follows:

- - SAEs that occur > 30 days after the last administration of investigational agent/intervention and have an attribution of possible, probable, or definite should be reported to Mayo Clinic (refer to **Section 10.2.2**).
  - For AEs occurring >30 days after the last administration of investigational agent/intervention, refer to **Section 10.2.1.1** for reporting requirements.

10.2.3.2 Pregnancy and Pregnant Partner

If a subject of childbearing potential becomes pregnant, or a subject of reproductive potential fathers a child, while the subject is on protocol, report the pregnancy to Mayo Clinic as specified below.

NOTES: Pregnancies and/or lactations that occur after registration but before treatment allocation/randomization must be reported by the investigator if they cause the subject to be ineligible from continued participation on the trial.

Pregnancies and lactations that occur from the time of treatment allocation/randomization through 30 days following cessation of study intervention, or 30 days following cessation of treatment if the subject initiates new anticancer therapy, whichever is earlier, must be reported by the investigator.

10.2.3.2.1 Pregnancy

Immediately, upon the Investigator becoming aware of a pregnancy, the site must contact [[contact]](mailto:[contact]) for reporting instructions. Mayo Clinic Comprehensive Cancer Center FDA Coordination Team will follow-up with the investigator regarding additional information that may be required.

If any person becomes pregnant during the study, the investigator should attempt to obtain information regarding the birth outcome and health of the infant. If the outcome of the pregnancy meets a criterion for immediate classification as a Serious Adverse Event (i.e., a person of childbearing potential experiences a spontaneous abortion, stillbirth, or neonatal death or there is a fetal or neonatal congenital anomaly) the investigator will report the event as a Serious Adverse Event.

Pregnancy must be reported in an expedited manner as **Grade 3 “Pregnancy, puerperium and perinatal conditions - Other (pregnancy)”** under the Pregnancy, puerperium and perinatal conditions System Organ Class (SOC). Pregnancy should be followed until the outcome is known.

10.2.3.2.2 Pregnant Partner

If a subject’s partner becomes pregnant, the investigator should discuss obtaining information regarding the birth outcome and health of the infant from the pregnant partner. **Prior to obtaining private information about a childbearing person and their infant, the Investigator must obtain consent from the childbearing person and the newborn infant’s parent or legal guardian before any data collection can occur. A consent form will need to be submitted to the IRB for these subjects if a pregnancy occurs.**

NOTE: If informed consent is not obtained, no information may be collected.

The site must contact [[contact]](mailto:[contact]) for reporting instructions. Mayo Clinic Cancer Center FDA Coordination Team will follow-up with the investigator regarding additional information that may be required.

10.2.3.3 Death

A death occurring between the time of registration and ≤30 days after last dose of study treatment requires iMedidata Rave reporting regardless of causality. Attribution to treatment or other cause must be provided.

Reportable categories of Death

- Death Not Otherwise Specified (NOS): A cessation of life that cannot be attributed to a CTCAE term associated with Grade 5.
- Sudden death NOS: A sudden (defined as instant or within one hour of the onset of symptoms) or an unobserved cessation of life that cannot be attributed to a CTCAE term associated with Grade 5.
- Death due to progressive disease that cannot be attributed to a CTCAE term associated with Grade 5 should be reported as **Grade 5 “Disease progression” under the SOC of “General disorders and administration site conditions.”** Evidence that the death was a manifestation of underlying disease (e.g., radiological changes suggesting tumor growth or progression: clinical deterioration associated with a disease process) should be submitted.
- All other causes of “Death” must be attributable to a Grade 5 CTCAE term.
- Death will only be expeditiously reported if it occurs ≤ 30 days after the last study dose of radiation AND the death is deemed possibly, probably or definitely related to the radiation treatment by treating provider and/or site PI. All other deaths will be reported during continuing review as part of the ongoing AE log if they meet reportable criteria above.

10.2.3.4 Secondary Malignancy

- A secondary malignancy is a cancer caused by treatment for a previous malignancy (e.g., treatment with investigational agent/intervention, radiation or chemotherapy). A secondary malignancy is not considered a metastasis of the initial neoplasm.
- All secondary malignancies that occur following treatment with an agent under an IND will be reported. Three options are available to describe the event:
- Leukemia secondary to oncology chemotherapy (e.g., Acute Myelocytic Leukemia [AML])
- Myelodysplastic syndrome (MDS)
- Treatment-related secondary malignancy
  - Any malignancy possibly related to cancer treatment (including AML/MDS) should also be reported via iMedidata Rave.

10.2.3.5 Second Malignancy

A second malignancy is one unrelated to the treatment of a prior malignancy (and is NOT a metastasis from the initial malignancy). Second malignancies require ONLY routine reporting via iMedidata Rave unless otherwise specified.

10.2.3.6 Protocol Violation/Deviation Reporting

The Mayo Clinic [[contact]](mailto:[contact]) inbox must be notified immediately, of any Major Deviation (defined in **Section 10.1.6**).

**Mayo Clinic Sites:** All Major and Minor deviations must be entered in PTrax immediately upon the study team becoming aware of the violation/deviation. Mayo Clinic staff are responsible for reporting to the Mayo Clinic IRB per IRB policy.

**External NON-Mayo Clinic Sites:** All deviations must be entered into the appropriate iMedidata Rave eCRF. Non-Mayo Clinic Sites are responsible to report to their local IRB per IRB policy.

### 10.3 Sponsor-Investigator Reporting

Per FDA, 21 CFR 312.32, Mayo Clinic will report SAEs and/or suspected unexpected serious adverse reactions as required to regulatory authorities, investigators/institutions, and IRBs/IECs in compliance with all reporting requirements according to local regulations and Good Clinical Practice.

Mayo Clinic Cancer Center (MCCC) FDA Coordination Team will assist the sponsor-investigator in the processing of expedited reports (i.e., IND Safety reports, deviations, dosing errors, pregnancy, etc.), as appropriate.

The MCCC FDA Coordination Team will report SAEs to the pharma partner(s) per contract.

## **11.0 Treatment Evaluation/Measurement of Effect**

See Appendix III: Criteria for Response Assessment

11.1 Patients will be evaluated at baseline, then according to the Assessment Schedule (**Section 4.0**, toxicity assessment, adverse event collection, PET/CT evaluation per Lugano criteria, survival, etc.)

11.2 At the time of reevaluation, patients will be classified in the following manner:

- No evidence of disease
- Recurrence of disease. Consider biopsy of the site, salvage systemic therapy, etc. per treatment team discretion.

11.3 The radiographic site of progression (or failure) will also be collected and classified as either:

- Local: centered within the 95% isodose line of the treatment plan.
- Distant: outside the 95% isodose line of the treatment plan.

11.4 Response assessment

Schedule of evaluations: All patients are required to receive a PET/CT scan at baseline. Post-treatment tumor recurrence will be monitored with follow-up PET/ CT scans to assess tumor response based on Lugano criteria until local progression within radiation field or death (or up to 24 months after the completion of radiation treatment) at which point participants will go to survival follow-up. Patients who did not test FDG negative at baseline are strongly recommended to receive a PET/CT or CT if PET/CT is not done, 3 months after treatment as part of post-treatment follow-up. Patients will receive a follow-up CT scan at 6 months post-treatment and will continue to do so every 6 months at clinician’s discretion. For patients without measurable disease on baseline PET/CT or CT (eg cutaneous lymphoma) follow up imaging is not required and response will be based on clinical exam.

Patients with gastric lymphoma will receive an endoscopy prior to registration. Post-treatment tumor recurrence will be monitored with follow-up endoscopies at 3 months and every 6 months per clinician’s discretion after treatment.

The Lugano criteria is outlined in Appendix III. For gastric lymphoma, additional information regarding pathologic response will be provided via endoscopy.

[figure not shown]

## Table from Olsen *et al* see reference 17.

## **12.0 Descriptive Factors**

• Age (≤60 years and >60 years)

• Sex (M/F/Unknown/Intersex)

• Diagnosis/Histology (Follicular I/II, Follicular IIIA, Marginal Zone/Malt, Other)

• Reason for radiotherapy (curative/palliative)

• Eastern Cooperative Oncology Group (ECOG) performance status (0, 1, 2 vs. 3)

• Ann Arbor stage (Stage I/II vs. III/IV/relapse/refractory)

• Target site maximum diameter (>6 cm vs. ≤6 cm)

• Lactate dehydrogenase at registration/first treatment (≤ULN vs. >ULN)

• Extranodal site (yes/no)

• Previous radiation therapy (yes/no)

• Previous chemotherapy (yes/no)

• Number of sites treated in this trial (≤2 or >2)

## **13.0 Treatment/Follow-up Decision at Evaluation of Patient**

13.1 Those patients who will not receive any radiation treatment or who will receive radiation treatment elsewhere will go off study per **Section 13.7**.

13.2 Patient who are CR, PR, or SD will continue to obtain PET or CT scans at each clinically indicated follow up for up to 24 months after the completion of radiation treatment.

13.3 Patients who develop PD or withdraw from further follow up assessments will be followed for event monitoring only per **Section 4.0**.

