Event monitoring is the period when the participant is no longer following the protocol test schedule due to disease progression and/or the patient was started on a new non-study anti-cancer treatment. During Event Monitoring, the data collection schedule is dictated by the protocol, but the visit schedule is determined by clinical practice at each participating site. During the Event Monitoring Phase of the study, the participant is being monitored for key study events such as new non-study anti-cancer treatments given, new primaries, and death. Samples from biospecimens collected in the course of clinical care may be requested but cannot be required of the participant.

##

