### 16.3 Secondary

The following definitions are used for the secondary endpoints of interest:

• Response rate at 3 months post radiation treatment: is reported as a proportion calculated as the number of cases with complete response (CR) or a partial response (PR) at 3-month post radiation imaging based on Lugano criteria divided by the total number of treated patients. Treated patients who do not have a 3-month evaluation will be classified as a non-response.

• Local control rate at 2-years: defined from the time of registration to local relapse that overlaps the treated site (95% isodose line).

• Patient Reported Outcomes/Quality of life: FACIT-Fatigue given as SOC for Lymphoma patients within 3 months after end of radiation treatment will be used as outlined in section 4.0 and 7.0.

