### 16.5 Statistical Design

16.5.1 Decision Rules

16.5.1.1 A two group χ^2^ test of equal proportions in acute adverse events will be conducted to determine the efficacy in acute toxicity reduction within the treatment arm. If the p-value of the statistical test is less than 0.10 then the treatments will be considered significantly different in the direction of the point estimates. Therefore, a significant difference in the direction of the experimental arm will deem the treatment favorable and worth consideration in future trials. If the test is non-significant then the experimental arm will not be considered significantly different in toxicity profile and therefore, not considered for future trials. It is also important to consider the local control rate when deciding whether to pursue further study. In the FoRT trial, the 2-year local progression-free rate was 94.1% after 24 Gy and 79.8% after 4 Gy. If the observed 2-year probability of local control is more than 7% inferior with 9 Gy versus 24 Gy, then we will not consider future trials. For example, if the 2-year local control rate is 94.1% after 24 Gy, and less than 87.1% after 9 Gy then we would not pursue further study.

16.5.1.2 Over Accrual: We will accrue approximately 10% over-accrual (112 total patients, 56 per arm) in order to ensure 102 evaluable patients as described in previous sections. The first 102 evaluable patients will be utilized for analysis of the primary endpoint.

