16.6.2 Secondary Analyses

16.6.2.1 Response Rate: All patients who were registered to the study and started treatment will be included in the response rate analysis. Response rate will be defined as the proportion of patients displaying response (PR or CR) at 3 months post treatment; patients who did not have a 3-month post treatment assessment will be considered a non-response. A chi-square test will be used to compare response rates between the two treatment arms. Absolute risk difference and relative risk will be calculated; 95% confidence intervals will be calculated using the score method.

16.6.2.2 Local control: All patients who were registered to the study and started treatment will be included in the local control analysis. A local recurrence event is any event defined as disease relapse occurring in the area treated before with radiation (anything included within the 95% isodose line). The local control interval will be defined as the number of days from end of radiation treatment until first local recurrence within 24 months post radiation treatment; censoring will occur at date of patient death or date of last disease evaluation (based on imaging and clinical exam). Local control rates will be estimated separately for the two treatment groups at 3-, 6-, 12-, 18, and 24-months post radiation treatment using the Kaplan-Meier method. Hazard ratio and 95% confidence interval for comparison of local recurrence between the two treatment arms will be estimated from a Cox proportional hazards model.

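### The 2-year local control that can rule out further trials rests on conflicting rules for follow-up after out-of-field progression, for what counts as local, and for when the clock starts

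*Protocol*

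**What the plan says.** **Decision.** Protocol 16.5.1.1 adds an observed-difference rule to the toxicity test. If 2-year local control is "more than 7% inferior with 9 Gy versus 24 Gy", no future trials are considered. Its example is 94.1% after 24 Gy against less than 87.1% after 9 Gy.

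**Follow-up.** Section 11.4 monitors with scans "until local progression within radiation field or death (or up to 24 months after the completion of radiation treatment"). Section 13.2 continues scans for patients with CR, PR or SD, and 13.3 says: "Patients who develop PD or withdraw from further follow up assessments will be followed for event monitoring only". Section 4.0 treats a patient in event monitoring as one "no longer following the protocol test schedule due to disease progression and/or the patient was started on a new non-study anti-cancer treatment". Visits then follow clinical practice. The events named are new anti-cancer treatment, new primaries and death, as examples in an open list.

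**Censoring.** Section 16.6.2.2 censors at death or at the last disease evaluation.

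**Local.** Section 11.3 classes a failure as local if it is "centered within the 95% isodose line of the treatment plan". Section 16.3 has local control "defined from the time of registration to local relapse that overlaps the treated site (95% isodose line"). Section 16.6.2.2 counts anything included within that line.

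**Clock.** Section 16.3 starts at registration. Section 16.6.2.2 uses the "number of days from end of radiation treatment until first local recurrence within 24 months post radiation treatment".

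**The concern.** Local control is a secondary endpoint, but it is the only efficacy measure that can stop development of the reduced dose. The rule compares a point estimate with a fixed limit, so which events are seen, and how they are classed, can settle the outcome.

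The follow-up conflict matters most. A patient whose first progression is outside the field stays under observation for local control in 11.4, but leaves the test schedule under 13.3 and 4.0. Such patients will not be rare: Section 1.0 says relapses after radiation alone were usually at unirradiated sites, and Section 3.1 admits any stage, including relapsed and refractory disease. An analysis plan cannot repair this later, because in-field status that nobody recorded cannot be analysed.

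The spatial conflict means the site classification collected under 11.3 does not match the endpoint defined in 16.3.

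**Working it through.** **Inputs from the protocol.** 94.1%, 87.1% and the 7-point limit (16.5.1.1); 51 per arm (16.5.4); 10-year PFS of about 50% in early-stage disease (1.0); treatment start up to 21 days after registration (6.7); treatment lasting 5 or 16 days, ±2 (4.0).

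**Assumed.** Distant progression by 2 years of 20 to 40%; a gamma frailty of variance θ = 1 or 2 shared by local and distant failure; constant baseline hazards; the same distant rate in both arms.

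**1. The plan's own figure.** 94.1 − 7 = 87.1%, which reproduces. One patient is 1/51 = 2.0 points.

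**2. One patient under both rules.** Suppose new disease appears outside the field at 6 months and an in-field relapse at 15 months. Under 11.4 this is a local event at 15 months. Under 13.3 and 4.0 the schedule ends at 6 months. If no later evaluation is recorded, 16.6.2.2 censors the patient there.

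**3. A rate anchored in the document.** At constant hazard, 10-year PFS of 50% gives 1 − 0.5^(2/10) = 0.129, or 13% progression by 2 years, here all treated as distant.

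**4. What Kaplan-Meier reads when censored at distant progression.** With 24-month cumulative hazard H(p) = [(1 − p)^(−θ) − 1]/θ, for local (L) and distant (D) failure, the estimate tends to

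S = [1 + θ(H_L + H_D)]^(−H_L / (θ(H_L + H_D))).

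Example, θ = 1 and 13% distant:
- H_D = 0.1487.
- 24 Gy: H_L = 0.0627, S = 1.2114^(−0.0627/0.2114) = 0.945.
- 9 Gy: H_L = 0.1481, S = 1.2968^(−0.1481/0.2968) = 0.878.
- Deficit: 6.6 points.

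Deficit read when the true deficit is 7.0 points:

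| Distant progression by 2 years | Independent | θ = 1, formula (simulated) | θ = 2, formula (simulated) |
|---|---|---|---|
| 13% | 7.0 | 6.6 (6.7) | 6.4 (6.3) |
| 20% | 7.0 | 6.4 (6.5) | 6.0 (6.0) |
| 30% | 7.0 | 6.1 (6.1) | 5.4 (5.4) |
| 40% | 7.0 | 5.7 (5.7) | 4.7 (4.6) |

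A repeat simulation with 1,000,000 per arm gave 4.65 for the last cell. Under independence nothing is biased, though 6 to 22% of local failures go unseen across these rates.

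**5. Effect on the decision.** With complete data, 51 per arm and a true 87.1% against 94.1%, the exact binomial chance of an observed deficit above 7 points is 0.505. In simulated trials at 30% distant progression and θ = 2, it falls from about 51% to about 35%.

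**6. Spatial rules side by side.**

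| Relapse | 11.3 | 16.3 | 16.6.2.2 |
|---|---|---|---|
| Wholly inside the line | local | local | local |
| Overlaps, centred inside | local | local | unclear |
| Overlaps, centred outside | distant | local | unclear |

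The size of this effect cannot be computed: the protocol does not give the share of marginal relapses.

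**7. Time origin.** The two origins differ by up to 21 + 5 = 26 days (9 Gy) or 21 + 16 = 37 days (24 Gy). At constant hazard λ = −ln(S)/730.5 per day, 26 to 37 days moves control by 0.20 to 0.29 points at 94.1% and by 0.43 to 0.61 points at 87.1%. The deficit itself moves by about 0.43 − 0.29 = 0.14 points.

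**The case against.** A reader might infer that local control is simply not followed after any progression. The protocol does not support that. Section 11.4 does follow it, the event list in 4.0 is open, imaging is standard of care, and 18.4 asks for documents supporting progression after therapy. What stands is a contradiction: after progression at any site, 13.3 and 4.0 require no scheduled treated-site assessment and do not name local relapse as an event.

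A reader might also infer that the censoring necessarily favours the reduced dose. It does so only if local and distant failure are positively dependent. The frailty is assumed, and so is any distant rate above 13%. At 13% the shift is under 1 point, less than one patient. This objection holds and limits the claim.

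Continued follow-up has its own difficulty. Section 11.2 mentions salvage systemic therapy at recurrence, which may also act on the treated site. If salvage is assumed to cut later local hazard by 50 to 80%, full follow-up reads the 7-point deficit as 6.7 to 5.9 under independence and 6.5 to 5.0 with frailty variance 1, a distortion of similar size. The remedy therefore has to deal with new treatment.

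Finally, the wording in 16.6.2.2 can be read as any part of the relapse inside the line, which would agree with 16.3. The firm spatial conflict is between 11.3 and 16.3.

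**Conclusion.** The contradictions are real and should be fixed. They concern a secondary endpoint that can end development, and the primary toxicity comparison is untouched.

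The follow-up conflict carries most weight. Its effect runs from none (independence), through less than 1 point at the document-anchored 13%, to a true 7-point deficit reading about 4.65 at the extreme of the assumed range. These figures show sensitivity to assumed inputs and are not a prediction. The spatial conflict is certain in the text but unquantified. The origin conflict is also certain, and numerically minor.

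**What to change.** - **Follow-up (4.0, 11.4, 13.3).** After out-of-field progression, keep recording in-field status from routine imaging or examination to 24 months, and name local relapse as a monitored event.
- **New treatment (16.6.2.2).** Record the start date of any new anti-cancer treatment. Report local control twice: counting all in-field relapses, and censoring at new treatment.
- **Spatial rule (11.3, 16.3, 16.6.2.2).** Use one rule throughout. The *overlaps* wording classifies every relapse.
- **Origin (16.3, 16.6.2.2).** Use one origin, and state it in the 2-year rule in 16.5.1.1.

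The cost is amendment wording and a little extra abstraction from standard-of-care records, with no new procedures. It is best done while follow-up is running, since unrecorded in-field status may not be recoverable later.
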